### Phase III: Programme development and implementation

The perspective for this part of the programme is the continued use of the ecological framework which recognises that individuals' behaviours are determined by a web of factors that operate at multiple levels [27]. We aim to reduce health inequalities by targeting health-related problems defined by community members themselves. We will use Intervention Mapping (IM) which is a stepwise procedure for the systematic development, implementation and evaluation of health promotion programmes using the social ecological approach (see Figure 1) [28]. In line with ecological models of health behaviour, IM distinguishes between individual and environmental determinants of health behaviour and is an integrative problem driven approach to explore mediators of behaviour change and to identify potential behaviour change strategies. IM is a systematic way to proceed from knowledge about behavioural determinants to specific change goals, and subsequently to intervention methods and strategies, based on the population intervention matrices. Such matrices finally develop into an "intervention map" that makes the translation of objectives for change to actual intervention activities.

**Figure 1 F1:**
[figure not shown]
**Intervention Mapping protocol **[28].

This phase provides the foundation of the intervention by specifying who and what will change as a result of the intervention. The aim of this phase is to establish a set of matrices of selected ecological levels (i.e. individual, interpersonal/family, community, organisational, policy through to societal) that combines performance objectives for each level with selected determinants required to produce change objectives. This process will define what needs to be achieved in order to enable changes in behaviour or environmental conditions that will increase physical activity levels. Objectives beyond the individual will include environmental agents selected at each ecological level.

Members of the community organised into "working groups" will be asked to formulate specific programme objectives for each of the key environmental issues related to lifestyle choices, namely (i) individual, (ii) interpersonal/family (iii) social factors, (ii) organisational factors, (iii) policy, and prioritise these based on importance and desirability to change leading to a local health action plan (key activities and actions). For each priority area they will create a matrix of change objectives for each level of intervention planning (individual, interpersonal, organizational, community, and societal) by crossing performance objectives with determinants.

Our approach emphasizes the importance of local relevance and context. Thus the precise health issues and intervention(s) over the 2 years to be addressed cannot be defined *a priori*. The community-led intervention(s) will be facilitated by the CDWs and neighbourhood Area Implementation Teams working in the three intervention Wards.

Programme implementation will be resourced by Stoke-on-Trent Primary Care Trust. We will endeavour to incorporate the intervention programme within mainstream healthcare delivery through local commissioning via the PCT in order to ensure sustainability. We will embed successful elements of the intervention within organisations' routines, and by capacity-building in the recipient communities. As part of the intervention we will use programme "champions" recruited from volunteers in the community and trained to help support and facilitate the adoption of programme objectives.

Throughout the intervention period, we will develop an evaluation framework based on the Logic Model [29] designed to enable partners to monitor programme activities and to assess the extent to which those activities, independently or in combination, influence desired intervention goals. Key stakeholders will be involved to ensure that the results or outcomes are relevant to recipients, funders and policymakers. We will use mixed methods (qualitative and quantitative) to assess the impact of a systematic effort by residents to engage in a collaborative approach leading to culturally sensitive and appropriate action. It will not be feasible to evaluate, with full rigour, all of the individual elements that make up this multi-factorial, multi-agency approach, in which several smaller components are combined to yield an overall effect. Where we are able to do so, we have designed the programme element with sufficient power to detect expected differences in the physical activity levels.

### Phase IV

#### Primary and secondary outcomes

##### Primary outcome measures

The primary outcome measure of effectiveness of this approach will be the change in physical activity in the three areas compared with the other wards in Stoke-on-Trent (using the Active People Survey [16]). The study is designed to detect a 10% increase (intervention areas vs. the rest of Stoke-on-Trent) in the proportion of participants reporting an increase in physical activity, made up of those initially engaging in some activity who increase this to the level recommended to derive health benefit and those initially doing little or no activity who increase to doing some regular activity. Objective measures of physical activity will be used for a random sub-sample of respondents to the community survey using 7-day accelerometry (ActiGraph) as a check on self-reported physical activity measures [26].

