### Study population

Our study will include targeted lower level Super Output Area (SOAs), the smallest geographical unit for which census information is available in the UK, in three deprived wards in Stoke-on-Trent, UK (Meir, Burslem South and Bentilee) that are similar with regards to socio-economic status (i.e. in the most deprived 40% of the 2007 Index of Deprivation - (IMD)) and are not undergoing major housing regeneration over the next 3 years. A lower level Super Output Area consists of a population size of ~1,500. These spatial units were chosen because they provide an approximate neighbourhood level of analysis due to their population size and are tied to UK Census data.

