### Proposed sample size

Sample size calculations for the independent survey sample are based on Cohen's arcsine transformation for estimating differences between proportions [15], where;

$$\begin{array}{c} \varphi =2\;\text{arcsine}\left(\sqrt{\text{p}}\right)\\ \text{h}=\left|\varphi_{1}-\varphi_{2}\right| \end{array}$$

P is the proportion and h is the effect size to be detected. The best available estimate of the population proportion currently active at the recommended level was that taken from Active People Survey 2 [16] (sub-group NS-SEC 6-8 i.e. those most closely matching the demographic profile of the target population for this study), which was 7.5%. Based on our previous research [17], we anticipate being able to achieve a 10% increase in this population proportion i.e. 17.5% after the community-led intervention. Using Cohen's arcsine formula this gives a standardised effect size of 0.273. Assuming a false positive error rate of .05, statistical power of .8 and this standardised effect size, we have calculated a required sample size of 283 participants at follow-up. Further, assuming a survey response rate of 10% (expected to be low for this target population) the issued sample size will be 2830 surveys.

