### Community survey

Addresses will be selected from the postcode address file representing all of the targeted streets within each ward included in the study. Postal questionnaires will be sent to a random sample of addresses within the study area for each of the Lower Super Output Areas (LSOA). For each household a random date will be generated and the adult whose birthday falls closest to this date will be asked to complete the questionnaire (intended to select persons within the household with equal probability).

As an incentive, all participants will be entered in to a prize draw for £200 of High Street vouchers if they complete and return the questionnaire.

All respondents at wave 1 would be issued again at wave 2 (at 24 month follow up). This gives sufficient power to detect the expected 10% difference in population proportions. Since only one person is being randomly selected at addresses which have more than one resident aged 16+, at the analysis stage we would apply weights (equal to the inverse probability of selection) to adjust for this.

The self-report questionnaire will include validated and reliable questions on physical activity [21], behavioural intentions and behavioural change [22], perceived health - SF12 [23], perceptions of the local neighbourhood for physical activity (Neighborhood Environment Walkability Scale) [24], social capital [25] and socio-demographic information (gender, age, ethnicity, education level, household tenure). The questionnaire and survey procedures will be fully piloted before the main fieldwork for wave 1 and for any changes or additional questions at wave 2 (at follow up).

In addition to the survey a random sub-sample of 100 adults from each of the three Wards will be asked to wear an accelerometer (GMT1) for 7 consecutive days to measure physical activity levels [26].

Results from the objective GIS mapping and community survey will be used as the basis of community consultation.

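### The primary outcome compares three selected deprived wards with all other Stoke wards, unmatched, without saying which survey measures which area or ruling out a comparison of levels

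*Protocol article*

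**What the plan says.** All references are to the protocol article.

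- **Primary outcome measures** sets the contrast: change in the three areas "compared with the other wards in Stoke-on-Trent (using the Active People Survey [16"]). The design target is then restated as a 10% increase, "intervention areas vs. the rest of Stoke-on-Trent". No matching or restriction of the other wards is given.
- **Study population** selects the intervention wards as similar in socio-economic status, within the 40% most deprived on the 2007 index, and as areas that "are not undergoing major housing regeneration over the next 3 years".
- **Community survey** describes the study's own data collection: "Postal questionnaires will be sent to a random sample of addresses within the study area". On the instrument: "The self-report questionnaire will include validated and reliable questions on physical activity [21"]. Wave 1 respondents are approached again at 24 months.
- **Proposed sample size** takes its 7.5% baseline rate from the Active People Survey, "sub-group NS-SEC 6-8 i.e. those most closely matching the demographic profile of the target population for this study". It asks for 283 participants at follow-up and assumes 10% response.
- **Study design** describes a pre-post case study and names no control. **Data analysis** nevertheless plans a chi-squared test of the distribution of activity categories between intervention and control areas, with multinomial logistic regression for odds ratios.

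**The concern.** There is no randomisation, so attribution rests on the comparator showing what would have happened in the intervention wards without the programme. Three features weaken that.

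1. **Population.** The intervention wards passed two filters that the comparator wards did not. Regeneration matters in particular, because it may alter the built environment that the study aims to change. A comparator under regeneration, or less deprived, may have a different two-year trend.
2. **Measurement.** The two sides may be measured by different surveys, and nothing says that the activity items are the same.
3. **Analysis.** The outcome is worded as change, but the planned test is worded as a comparison of distributions between areas.

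At stake is the effect size, which Study aims says will be used to design a larger controlled trial if findings are positive. A contrast that mixes background trend with programme effect would carry into that decision.

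**Working it through.** **The plan's own figures.** The issued sample follows from the required one: 283 / 0.10 = 2830. The required number itself does not reproduce. With h = |2 arcsin(√0.175) − 2 arcsin(√0.075)|, h = 0.308, not 0.273. At two-sided 0.05 and 80% power, n per group = 2(1.960 + 0.842)²/h² gives 165 for h = 0.308 and 211 for h = 0.273. That is a separate matter, and this point does not depend on it. What matters here is that the calculation contains only two proportions, 7.5% and 17.5%. It has no term for change in the comparator.

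**What the contrast estimates.** Let I1 and I2 be the proportions active in the intervention wards at baseline and follow-up, and C1 and C2 those in the comparator.

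- Contrast of change: D = (I2 − I1) − (C2 − C1) = programme effect + (background trend in the intervention wards − background trend in the comparator) − spill-over into the comparator + any change in the measurement difference between waves.
- A measurement or population offset that is constant over time appears in both C1 and C2 and cancels from D.
- Contrast of levels at follow-up: L = I2 − C2. Here the same constant offset does not cancel.

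With the planned rates, I2 − I1 = 17.5 − 7.5 = 10 points, so D = 10 − (C2 − C1). Each point by which the background trends differ moves D by one point. The document gives no comparator rate, trend or number of respondents, so neither the bias nor the resulting power can be calculated.

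**Which survey measures which area.** There are two readings.

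- *Postal survey for the intervention wards, Active People Survey for the rest.* This fits the sample-size section and the plan to check self-report by accelerometry in community-survey respondents. The contrast then crosses two surveys whose activity items are cited to different sources, and the postal survey expects about 10% response.
- *Active People Survey for both areas.* Measurement is then common, but the 283-person survey does not supply the primary outcome, and the accelerometry check is made on respondents who do not contribute to it.

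The text does not settle this, and either reading needs a correction.

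**Change or level.** Primary outcome measures says change, and describes participants moving up an activity category. Data analysis tests distributions of activity categories between areas. If those are categories of change, the test could fit the outcome, but the section does not say so and contains no time term. A comparison of levels is therefore not excluded.

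**The case against.** **The outcome is already a change.** This largely stands: a constant offset in level cancels. A reader might infer that any difference in activity level between the areas biases the primary result directly. The outcome wording does not support that; only the loosely worded chi-squared test leaves it possible. Differing trends do not cancel under either analysis.

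**The instruments may be the same.** A reader might infer that the two surveys certainly use different activity questions. The documents show only two citation numbers, and the sources are not at hand. What can be said is that identity of the items is not stated.

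**NS-SEC 6-8 was never offered as a comparator.** Correct: it supplied a planning rate. The intervention sample is all adults at random addresses, and occupational class is not among the listed socio-demographic items. Restricting the comparator alone to that sub-group would create a new mismatch.

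**Contamination is conjecture.** A reader might infer that the programme reaches the comparator wards and pulls the contrast toward zero. Every ward has an implementation team tied to the same council and Primary Care Trust, the plan seeks to "incorporate the intervention programme within mainstream healthcare delivery through local commissioning via the PCT", and an advisory group is to help with policy change. But development workers are dedicated to each area, delivery is by teams in the three wards, and no section says that other wards receive the programme within 24 months. Spill-over is a limitation of unknown size, not a demonstrated bias.

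**It is a pilot.** True, and effectiveness is left to a later cluster randomised trial. That lowers the stakes but does not remove them, since this study's effect size informs that trial.

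**Conclusion.** The point holds in this form: the comparator is unrestricted although the intervention wards were selected on two criteria, the data source for each area is not fixed, and the planned test does not match an outcome worded as change. Followed as written, differences in trend and in measurement could be mistaken for a programme effect.

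No numerical bias or loss of power can be attached. Either would need comparator rates, trends, respondent numbers or a spill-over fraction, and the documents give none. The net direction is also open: spill-over would dilute the contrast, while population and survey differences could act either way. The conclusion assumes only that deprivation and regeneration can affect two-year trends in activity, and that the full protocol does not fix the comparator more narrowly than the article states. The changes are cheap and should be made before wave 1 fieldwork.

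**What to change.** 1. In Primary outcome measures, restrict the comparator to Active People Survey respondents in other Stoke wards that meet the Study population criteria: the same deprivation band and no major housing regeneration. The plan must already separate respondents by ward, so this adds a filter only. Use NS-SEC 6-8 only if occupational class is also collected in the postal survey and the same restriction is applied to the intervention sample.
2. Carry the Active People Survey activity items, word for word, in both postal waves, and state which survey measures each area. The questionnaire is to be piloted anyway, so the items can be settled then.
3. In Data analysis, test the difference in change between areas (an area-by-time term) instead of a cross-sectional distribution, so that it agrees with the primary outcome.
4. Acknowledge possible spill-over through shared city agencies as a limitation.

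The cost is fewer comparator respondents and so a wider interval, plus a few more questionnaire items. How many other wards would qualify cannot be read from the article and should be checked before the restriction is fixed.

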### Study design

Case study pre-post test intervention in three electoral Ward areas of similar socio-economic deprivation [14] in a deprived inner city in the UK with an estimated population of ~10,000 adults.

Targeted communities in these wards will take part in an intensive community-led project, designed to engage its residents in the development and delivery of a range of health related interventions over a period of 2 years. The intervention will:

1. use community participatory research to build an effective community partnership in order to engage community residents, and strengthen community involvement and participation

2. use partnership consensus to identify, prioritise and design intervention(s) related to specific health disparities (and their relevant environmental determinants and mediators)

3. recruit local residents and Third Sector organisations to help with the delivery and sustainability of the target intervention(s)

4. establish local systems for ongoing monitoring and evaluation of the intervention

5. establish a local Public Health Advisory Group comprised of members from cross-government departments (e.g. urban planning, architecture, health, police and transport) to help facilitate policy change

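### The claimed power for wards versus the rest of the city comes from a before/after calculation on a different endpoint, with no comparator in it

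*Protocol article*

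**What the plan says.** Under Study design, the protocol article describes a "Case study pre-post test intervention in three electoral Ward areas of similar socio-economic deprivation". The Research hypothesis likewise predicts a rise in the active share of the target population after two years and names no comparator.

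Proposed sample size follows that line. The starting value is 7.5%: "The best available estimate of the population proportion currently active at the recommended level was that taken from Active People Survey 2", in the sub-group closest to the target population. The target is then set: "we anticipate being able to achieve a 10% increase in this population proportion i.e. 17.5% after the community-led intervention". The calculation continues "this gives a standardised effect size of 0.273" and "Assuming a false positive error rate of .05, statistical power of .8 and this standardised effect size", and ends "we have calculated a required sample size of 283 participants at follow-up". No second area appears in it. The Community survey section adds that wave 1 respondents are re-issued at wave 2, and says this gives enough power for the expected 10% difference.

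Primary outcome measures sets a different target. The outcome there is change in the three areas compared with the city's other wards, using the Active People Survey. The power claim is "The study is designed to detect a 10% increase (intervention areas vs. the rest of Stoke-on-Trent"), and it concerns the proportion of participants whose activity increases. That group combines people who step up to the recommended level with people who move from little or none to some regular activity. Data analysis then plans a chi-squared test of activity categories between intervention and control areas.

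**The concern.** A power statement belongs to one endpoint and one contrast. Here the endpoint changes from being active at the recommended level to having increased activity, and the contrast changes from before versus after to wards versus the rest of the city. The between-area comparison also carries the comparator's sampling error and depends on the comparator's rate, and neither enters the calculation.

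The article says its results will decide whether a larger controlled trial follows and will inform its design. If the city comparison is null and is read as coming from an 80%-powered study, the approach could be dropped on evidence of unknown strength. If the ward-only rise is read as the primary result instead, any city-wide trend would be credited to the intervention.

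**Working it through.** **1. What the stated inputs give.** From Proposed sample size: p1 = 0.075, p2 = 0.175, alpha 0.05 (sidedness not stated), power 0.80, stated h = 0.273, stated n = 283.

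- h = |2 arcsine(√0.075) − 2 arcsine(√0.175)| = |0.5548 − 0.8632| = 0.308, not 0.273.
- n per group = 2(z_alpha + z_power)²/h². Two-sided, (1.960 + 0.842)² = 7.849, so n = 2 × 7.849/0.273² = 211, or 165 at h = 0.308. One-sided, the figures are 166 and 130.
- The figure of 283 is not reproduced at 80% power. With 283 per wave and independent waves, before/after power is Φ(h√(283/2) − 1.96) = 90% at h = 0.273 and 96% at h = 0.308. So the pairing of 80% with 283 does not fit even the before/after contrast.

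**2. The two targets side by side.**

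| | Proposed sample size | Primary outcome measures |
|---|---|---|
| Endpoint | active at the recommended level | activity has increased |
| Contrast | same population, before and after | three wards vs rest of city |
| Comparator rate, size, variance | none | not stated |

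**3. Illustration A: difference in change in the proportion active.** Assumptions: 283 ward respondents per wave, m comparator respondents per wave, wards rising from 7.5% to 17.5%, comparator flat at rate c, independent samples, two-sided 0.05, no weights or clustering.

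SE² = (0.075 × 0.925 + 0.175 × 0.825)/283 + 2c(1 − c)/m; power = Φ(0.10/SE − 1.96).

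For c = 7.5% and m = 283: SE² = (0.069375 + 0.144375 + 0.13875)/283, so SE = 0.0353 and power = Φ(0.87) = 81%.

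| Comparator rate c | m = 100 | m = 200 | m = 283 | m = 1,000 |
|---|---|---|---|---|
| 7.5% | 58% | 75% | 81% | 92% |
| 15% | 41% | 60% | 69% | 88% |
| 20% | 36% | 54% | 63% | 86% |

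**4. Illustration B: two-group comparison of the proportion increasing.** Assumptions: 283 per group, a 10-point difference, comparator rate c, two-sided 0.05.

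SE² = [c(1 − c) + (c + 0.1)(0.9 − c)]/283; power as above.

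- c = 20%: SE = 0.0362, power 79%.
- c = 30%: SE = 0.0399, power 71% (70% with a pooled null variance).
- c = 40%: SE = 0.0416, power 67%.

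The values of c and m, and the 283 in the comparator group, are assumptions. The article gives none of them.

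**The case against.** Three objections have weight.

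First, a reader might infer that the primary comparison must be a difference in change built from four proportions, and hence that 283 is too few. The text does not settle this. Classing each re-surveyed person by whether activity rose gives one proportion per area, and the planned chi-squared test is also a two-group comparison. Illustration B covers that reading.

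Second, low power is not shown. The wards' waves re-survey the same people, so positive within-person correlation would raise power: with an assumed correlation of 0.5 in the wards and a comparator flat at 7.5%, the figure at m = 283 goes from 81% to 92%. A large comparator sample would also lift power above 80%. Working on the arcsine scale gives lower values (63% or 74% at m = 283, for h = 0.273 or 0.308), so the scale matters too. In the other direction, 7.5% was chosen to match the deprived target population and may not describe the rest of the city, and clustering and the planned selection weights are ignored throughout.

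Third, this is a pilot reported in a condensed article, and the comparator sample size could reasonably sit in the full protocol. Its absence alone would be no fault. What remains is that the article makes a positive design claim and prints a calculation for a different endpoint and contrast. No later document can make that calculation support the claim.

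**Conclusion.** The point holds as an inconsistency in the primary power claim. The article's only calculation addresses neither the endpoint nor the comparison named under Primary outcome measures, so its 80% does not apply there. The actual power cannot be determined from the document. Under the stated assumptions it lies between about 36% and 92% for a difference in change (comparator flat at 7.5% to 20%, 100 to 1,000 respondents per wave). It lies between about 67% and 79% for a two-group comparison of the proportion increasing with 283 per group. A reader might conclude that the study is underpowered, but the document does not establish this: the result turns on the comparator's size and rate, on the within-person correlation, and on which contrast is meant.

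**What to change.** Choose one primary endpoint and one primary contrast, and state them identically under Study design, Research hypothesis, Proposed sample size, Primary outcome measures and Data analysis. Then take 283 ward respondents as fixed and report the power, or the detectable difference, for that contrast. Use the number of Active People Survey respondents available in the other wards and an explicit assumed comparator rate, shown over a range. Correct the effect size for 7.5% versus 17.5% (0.308) in the same calculation if that endpoint is kept. If the comparator figures cannot be obtained, remove the claim that the study is designed to detect a difference from the rest of the city.

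The cost is one calculation and some rewording. No extra respondents are needed. The restated power may be less favourable than 80%.

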### Research hypothesis

It is predicted that a community-led intervention (working with the community and multiple agencies collectively to achieve beneficial change in a given factor) will increase the proportion of the target population who are physically active (taking part on at least 3 days/week in moderate intensity sport and active leisure) by 10% more (after a two year of intervention).

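### The primary endpoint is stated in two incompatible ways: prevalence of being active in the hypothesis and sample size, share of people moving up an activity category in the outcome section

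*Protocol article*

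**What the plan says.** All places are in the protocol article.

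- **Research hypothesis.** The intervention "will increase the proportion of the target population who are physically active (taking part on at least 3 days/week" at moderate intensity), by 10% more after two years.
- **Proposed sample size.** The starting value is described as "The best available estimate of the population proportion currently active at the recommended level" and is 7.5%. The target follows: "we anticipate being able to achieve a 10% increase in this population proportion i.e. 17.5% after the community-led intervention". The 10% is therefore 10 percentage points of a prevalence.
- **Primary outcome measures.** The first sentence names the change in physical activity in the three areas, "compared with the other wards in Stoke-on-Trent (using the Active People Survey [16"). The next sentence says what the study is designed to detect: a 10% increase, intervention areas against the rest of the city, "in the proportion of participants reporting an increase in physical activity, made up of those initially engaging in some activity who increase this" to the recommended level, together with "those initially doing little or no activity who increase to doing some regular activity".
- **Community survey.** Questionnaires go to addresses in the study area, and wave 1 respondents are surveyed again at 24 months. No repeat measurement of the same people is described for the comparator.
- **Data analysis.** A chi-squared test compares the distribution of activity categories between intervention and control areas, and multinomial logistic regression gives odds ratios for the categories.

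**The concern.** The article gives two answers to the question of what a 10% gain means. One is the level of a population proportion. The other is the share of individuals who change in one direction. They differ in who is counted, in their base rate and in the data they need, so the same survey results could meet one and miss the other.

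The article plans to use the effect size to design a larger controlled trial if the findings are positive. If the effect comes from one quantity and the planning rate from the other, that trial would be sized wrongly. The claim that the study is designed to detect the second quantity also has no calculation behind it.

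**Working it through.** **1. Who is counted.** Call the prevalence A and the upward-mover share B. I take the 3-days-a-week level in the hypothesis and the recommended level in the sample size to be the same, as the article appears to.

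- From little or none to some activity: counts in B, does not change A.
- Active at the recommended level at both waves: counts in A, not in B.
- Falls from recommended to some: lowers A, ignored by B.
- Falls from some to little or none: changes neither.

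Suppose 10% of participants go from none to some and nobody else changes. Then B is 10% and A stays at 7.5%.

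**2. The plan's own calculation.** It uses h = |2 arcsin(√p1) − 2 arcsin(√p2)| and, for two groups, n per group = 2(z_α + z_power)² / h².

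- For 7.5% and 17.5%: h = |0.5548 − 0.8632| = 0.308. The article gives 0.273.
- With h = 0.273, two-sided 0.05 and 80% power: 2(1.960 + 0.842)² / 0.273² = 210.6, so 211 per group. The article gives 283.
- With h = 0.273 and 90% power: 282 per group, close to 283, but the stated power is .8.

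The stated h and n do not follow from the stated inputs, which is a separate point. What matters here is that every input is a prevalence. No base rate for B appears anywhere, so 283 is not derived for B.

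**3. B under no true change.** The article gives no category shares other than 7.5%, so the rest is assumed.

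- *Turnover by hand.* Take 50% little or none, 42.5% some and 7.5% recommended. Let 20% of each of the two higher groups drop one level and be replaced from below. B = 0.20 × 0.425 + 0.20 × 0.075 = 0.085 + 0.015 = 10%, and A stays at 7.5%. With 40% to 60% in the lowest group and 10% to 30% turnover, B runs from 4% to 18%.
- *Correlated repeat measurements.* Take a bivariate normal activity score with an upper cut at 92.5% and a lower cut at 40%, 50% or 60%. For wave-to-wave correlations of 0.8 down to 0.5, B is 13% to 21%, and the same share moves down. With the lower cut at 50%, B is 13.7% to 20.9%.

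These are levels within one area. If the same measure existed in both areas with the same turnover, they would cancel in the difference.

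**4. Power for B.** This depends on the comparator's share, which is not given. Assume 283 per group, two-sided 0.05 and a 10-point difference. Power = Φ(h√(283/2) − 1.960).

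| Comparator share (assumed) | n per group for 80% power | Power at 283 per group |
|---|---|---|
| 10% | 195 | 92% |
| 15% | 248 | 85% |
| 20% | 292 | 79% |
| 30% | 356 | 70% |
| 40% | 388 | 67% |

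The article does not say that 283 is per group and gives no comparator size, so the table shows dependence on the missing share and is not an estimate of the study's power.

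**5. Data needed.** A can be formed from separate cross-sections in each area. B needs each person's level at baseline and follow-up. The article describes that for the study wards only. The planned chi-squared test on category distributions matches an aggregate comparison such as A, not B.

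**The case against.** The best defence is that the outcome section means A and expresses it loosely. Its first sentence, on change in activity compared with the other wards, fits a difference in prevalence change, and the planned test of category distributions registers declines as well as gains. This stands as an argument for which definition to keep. It does not remove the conflict, because the next sentence states a different design target.

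A second defence is that a condensed article may leave out how the comparator is measured. That limits the claim: a comparator and a data source are named, and whether the Active People Survey follows the same people cannot be checked here. What can be said is that no person-level change measure is described for it. The choice between two stated targets is not a matter of condensation.

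Third, this is a pre-post pilot, which tempers the consequences but not the need for one endpoint.

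A reader might also infer three stronger things that the article does not support:

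- *That noise alone would reach the 10-point target.* The 13% to 21% is a within-area level, while the target is a difference between areas.
- *That the study is underpowered for B.* Only comparator shares of about 20% or more take 283 per group below 80%. At the no-change shares of 14% to 21%, power is 86% to 78%, which is roughly adequate.
- *That the survey uses different activity items from the comparator.* The article says only "validated and reliable questions on physical activity [21"]. A reference number other than [16] does not show that the items differ.

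**Conclusion.** The contradiction is real and concerns the primary endpoint, so it should be resolved before analysis. The hypothesis and sample size target a prevalence, while the outcome section targets a one-directional individual change. The second has no base rate, no sample size derivation and no described counterpart in the comparator.

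The conflict itself follows from the text and needs no assumption. The sizes do need assumptions: the upward share of 13% to 21% under no change (4% to 18% in the simpler turnover model) rests on assumed category shares and stability. It would mislead only if the comparator lacked a matching measure. The power range of about 92% to 67% rests on assumed comparator shares of 10% to 40% and 283 in each group.

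**What to change.** - In the primary outcome section, make the single primary endpoint the change in prevalence of moderate activity on at least 3 days a week, study wards against the rest of Stoke-on-Trent. This agrees with the hypothesis and sample size and suits the planned category comparison.
- Make sure that the postal questionnaire carries the Active People Survey item at both waves, if it does not already, so that the same quantity exists in both areas.
- Move the increase measure to a secondary outcome in the study-ward panel and report it as net change, the share moving up minus the share moving down.
- Apply the statement of what the study is designed to detect to the prevalence endpoint only.

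The cost is a rewording of one section and at most a slightly longer questionnaire, which is already due to be piloted. The fix assumes that the Active People Survey gives usable figures for the other wards at both time points. The article does not show this, so the sponsor should confirm it.
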